#### Study Outcomes

The data sources noted above enable us to examine a range of important study outcomes. Data on the time between a person’s first RAI-HC assessment and admission to a care home will come from provincial continuing care registries. Symptoms of depression will be assessed using the validated RAI-HC Depression Rating Scale [72], with scores ranging from 0 to 14 and a cut point of 3 or higher representing clinically meaningful depressive symptoms [72,73]. We will capture physical and cognitive decline, using validated RAI-HC scales [64]: the Activities of Daily Living Hierarchy (ADLh) Scale [74] and the Cognitive Performance Scale (CPS) [75]. Both scales range from 0 (no impairment) to 6 (maximum impairment), and our outcomes will be dichotomous, indicating any increase (vs no change or a decrease) between the previous and follow-up measurement in each of these scales. Using care practitioner claims data, we will generate rates of different types of primary and specialist care use (eg, family physician, specialists, nursing practitioner, and allied health providers). We will use the DAD and NACRS databases to generate rates of emergency department registrations, hospital admissions, and days in hospital (including alternative level of care) [43]. Rates will be stratified by day program use or nonuse pattern.

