#### Demographic, Social, and Health Characteristics

These will include older adults’ age, sex, marital or partnership status (population registries and RAI-HC), physical disability (ADLh Scale score of >3), and cognitive impairment (CPS score of >3). Available data sets include only a binary variable on biological sex (male or female) and no nonbinary information on gender identity. We will also include RAI-HC measures of caregiver availability (item G1e) and burden (items G2a-c). Finally, we will include 4 publicly available area-level measures from the Canadian Index of Multiple Deprivation [76,77]: residential instability (eg, housing insecurity, overcrowding, and frequent moves), economic dependency (high number of older adults, children younger than 15 years, and persons receiving government transfers), ethnocultural composition (eg, immigrants and racialized individuals), and situational vulnerability (eg, indigenous peoples, dwellings needing major repairs, and low education). Using Statistics Canada data, each measure is derived for 54,775 geographical dissemination areas, using 17 variables. Quintile-based ranks for each of the indices (1=least deprived to 5=most deprived) will be assigned to individuals based on their home’s postal code [77].

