#### Propensity Score–Matching Variables

To compare outcomes between day program attendees and nonattendees, we will use propensity score matching [78] (for details, see Statistical Analyses section). Propensity scores aim to ensure a similar distribution of baseline variables among treatment (day program attendees) and control (nonattendees)—akin to what random assignment aims to accomplish in randomized trials [78]. Since we lack evidence on differences between day program attendees and nonattendees, our objective 2 analyses will be key to informing the selection of the exact covariates that will form the propensity score. We will derive covariates for day program attendees from the RAI-HC day program eligibility assessment (index date). For each day program attendee, we will identify potential matches as nonattendees whose first RAI-HC assessment was completed within ±3 months of the attendee’s index date (ie, admission to long-term home care at about the same time). This RAI-HC assessment will provide the relevant covariates to enable propensity score matching with day program attendees as of their index date.

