Our first set of matching covariates will be RAI-HC variables used by health systems to determine day program eligibility [60,65,66]: physical functioning (ADLh Scale), cognition (CPS), behavioral symptoms (Aggressive Behavior Scale [79]), bladder or bowel continence (items I1, I3), availability of a caregiver (item G1e), and caregiver distress (items G2a-c). This will ensure that control participants are potentially eligible to a day program. Possible reasons for nonattendance include the lack of day program spaces, preference not to attend, inability to afford the required copayments, or not receiving a day program referral. Our experts assure us that the pool of potential matches far exceeds that of attendees, supporting the feasibility of this study and underscoring the lack of day program spaces. This approach excludes individuals whose care needs are either too low or too severe for day program eligibility, but it minimizes confounding by the matched variables and ensures comparable groups at baseline [80-82]. Finally, we will include a second set of matching covariates: health and social characteristics identified in objective 2 by which attendees and potentially eligible nonattendees differ and that overlap sufficiently between attendees and nonattendees (eg, age, sex, type or duration of publicly funded community care received before the matching index date, and deprivation indices).

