#### Objective 3: Assess Effects of Day Programs

To create a propensity score, we will run a logistic regression for each province with day program attendance or nonattendance as the dependent variable and adding matching covariates. We will use one-to-one matching (1 matched nonattendee for every attendee) [78]. We will use matching without replacement [85] and apply an optimal caliper matching algorithm [86]. As per best practice recommendations [87], we will use a caliper width of 0.2 of the SD of the propensity score’s logit. If this matching approach does not allow us to achieve a sufficient sample size, we will use propensity score quintiles for matching.

We will compare sample characteristics and study outcomes between attendees and nonattendees in every year and province, using bivariate statistical tests (eg, chi-square test or Fisher exact test for categorical variables, *t* tests, or ANOVAs for continuous variables, and their nonparametric equivalents if variables violate statistical assumptions). To assess the effect of day program exposure on time to care home admission, we will specify a multilevel time-to-event model with a health region–level random effect [88]. Health systems in each of the 3 provinces are divided into 5 health regions [89-91], and regional policies may cause clustering effects that our models must account for. Each model will include day program use or nonuse class as independent variable and will be adjusted for time-varying variables. These will include matching variables, if appropriate (ie, in case of group differences in matching variables over time or due to missing data) [80-82] and, if needed, additional covariates (eg, demographics, social determinants, medical or functional conditions, and non–day program community care). Covariates that differ between attendees and nonattendees with a *P* value of ≤.15 in the bivariate analyses will be considered for inclusion. We will add covariates stepwise, one-by-one, and remove those that cause collinearity issues or decrease model fit. As in objective 2, we will pool provincial effects statistically, using random-effects mixed regression models.

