Using GEEs and a similar approach as for the time-to-event models (including separate models in each province and statistical pooling of their effects), we will assess whether the other study outcomes differ by day program use or nonuse pattern. Models will include each study outcome of interest as a dependent variable, day program use or nonuse class and time of assessment as independent variables, and similar covariates (using the same stepwise approach) as the time-to-event models. Models will also include a random term to account for repeated measures within individuals. The choice of a link function will be informed by the nature of the variable and theoretical and empirical considerations. For example, the number of hospital, emergency department, or physician visits has been shown to follow a zero-inflated negative binomial distribution, sometimes requiring an offset for the natural logarithm of person-time [92]. For continuous outcomes (eg, days spent in hospitals), we will use an identity link function, and for dichotomous outcomes (eg, presence or absence of depressive symptoms), we will use a logit link function. All models will apply multiple imputation in case of missing data, which we expect to be small based on our previous work with the administrative health care data sources used in this study.

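### The plan does not commit to matching on, or adjusting for, baseline depressive symptoms and pre-index service use, so balance on these outcome baselines is not assured

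*Protocol article*

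**What the plan says.** All references are to the Methods of the protocol article.

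- **First matching set** (Propensity Score–Matching Variables): the variables used to decide day program eligibility, namely "physical functioning (ADLh Scale), cognition (CPS), behavioral symptoms (Aggressive Behavior Scale [79]), bladder or bowel continence (items I1, I3"), with caregiver availability and caregiver distress.
- **Second matching set** (same section): "health and social characteristics identified in objective 2 by which attendees and potentially eligible nonattendees differ", provided they overlap sufficiently. The examples are "eg, age, sex, type or duration of publicly funded community care received before the matching index date, and deprivation indices". The final list is left open: "our objective 2 analyses will be key to informing the selection of the exact covariates that will form the propensity score".
- **Objective 2 characteristics** (Demographic, Social, and Health Characteristics): age, sex, "marital or partnership status (population registries and RAI-HC), physical disability (ADLh Scale score of >3), and cognitive impairment (CPS score of >3"), caregiver availability and burden, and four area deprivation measures.
- **Mood outcome** (Study Outcomes): the DRS, with a "cut point of 3 or higher representing clinically meaningful depressive symptoms". Objective 3 models it as present or absent with a logit link.
- **Utilization outcomes** (Study Outcomes): rates of emergency department registrations, hospital admissions, hospital days, and primary and specialist care.
- **Outcome models** (Objective 3): each has "day program use or nonuse class and time of assessment as independent variables", with covariates chosen as for the time-to-event model. The rule there is "Covariates that differ between attendees and nonattendees with a *P* value of ≤.15 in the bivariate analyses will be considered for inclusion", followed by one-by-one addition and removal for collinearity or poorer fit. Models are fitted separately in each province and then pooled.

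**The concern.** In a matched cohort, the baseline value of an outcome is usually among its strongest predictors, and it may also influence who receives the service. Low mood or a recent hospital stay could plausibly affect referral or willingness to attend. The article says that attendees are either alone for long periods or have a caregiver who needs respite, that programs are mainly social and recreational, and that nonattendance may reflect preference or lack of referral.

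If attendees and controls differ at index on DRS or on recent service use, and neither matching nor the model removes the difference, it carries forward into follow-up. It would then be reported as a benefit or harm of day programs. Mental health and the use of emergency, acute and primary care are both named aims of objective 3.

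**Working it through.** The article gives no figure for baseline mood or prior service use, so there is nothing to reproduce. The sample size of 1327 concerns care home admission and is unaffected.

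**Step 1. Each outcome set against its baseline**

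| Outcome | Baseline in fixed matching set? | Baseline in listed objective 2 characteristics? | Form analysed |
|---|---|---|---|
| ADLh | Yes | Yes (>3) | Any increase from previous measurement |
| CPS | Yes | Yes (>3) | Any increase from previous measurement |
| DRS | No | No | Present or absent |
| Emergency, hospital, primary care use | No | No | Counts, rates or days |

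No baseline term is stated for the last two rows. Data Sources confirms that the data exist: mood is in the RAI-HC, and service use is in DAD, NACRS and claims.

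**Step 2. Routes by which the missing baselines could still enter**

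- *Second matching set.* Entry depends on a difference found in objective 2. That objective fits one model per characteristic, and neither variable is listed, so neither is certain to be examined.
- *Additional covariates.* These come from the right sources, but the examples given are geriatric syndromes, diagnoses and medications. Entry requires P≤.15 and survival of stepwise selection. The screen looks only at group difference, not at how strongly a variable predicts the outcome. Because it runs by province, a baseline could be adjusted for in one province and not in another before pooling.

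**Step 3. Illustration for mood (all inputs assumed, true effect null)**

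Let p be the proportion with DRS ≥3 at index, a the probability of DRS ≥3 at follow-up if positive at index, and b that probability if negative. Follow-up prevalence = p·a + (1−p)·b.

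With a = 0.60 and b = 0.12:
- p = 0.20: 0.120 + 0.096 = 0.216
- p = 0.25: 0.150 + 0.090 = 0.240; OR = (0.240/0.760)/(0.216/0.784) = 1.15
- p = 0.30: 0.180 + 0.084 = 0.264; OR = (0.264/0.736)/(0.216/0.784) = 1.30

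With a = 0.50 and b = 0.15:
- p = 0.20: 0.100 + 0.120 = 0.220
- p = 0.25: 0.125 + 0.1125 = 0.2375; OR = 1.10
- p = 0.30: 0.150 + 0.105 = 0.255; OR = 1.21

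Equal index prevalence gives OR 1.00. The sign reverses if controls are worse at index.

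**Step 4. Illustration for utilization (assumed inputs)**

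Let q be the proportion of frequent prior users and R their rate relative to others. Spurious rate ratio = [1 + q₁(R−1)]/[1 + q₀(R−1)], with q₀ = 0.20 in controls.
- q₁ = 0.25: 1.25/1.20 = 1.04 for R = 2, up to 1.75/1.60 = 1.09 for R = 4
- q₁ = 0.30: 1.30/1.20 = 1.08 for R = 2, up to 1.90/1.60 = 1.19 for R = 4

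**Step 5. Could such a bias reach significance?**

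To detect 24.0% against 21.6% with 80% power at two-sided .05, treating observations as independent: n per group = (1.96 + 0.84)² × (0.240×0.760 + 0.216×0.784)/0.024² ≈ 4,800. The article expects more than 20,000 attendees per year, so it could.

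**The case against.** The strongest reply has four parts.

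**The lists are open.** The objective 2 list says what it will include, the second matching set is given by example, and the exact covariates are deferred. One example, community care received before the index date, is itself a form of prior service use and is not in the objective 2 list. A reader might infer that mood and prior acute care are barred from the propensity score. The documents do not support that; nothing excludes them. This part stands in full.

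**Imbalance is not shown.** A reader might also infer that the groups start out unbalanced. No passage says so, the eligibility criteria mention neither variable, and the matched covariates may balance them in part. This stands too.

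**A large imbalance would probably be caught.** With 812 per group, the size of the earlier matched study cited in Sample Size Calculation, 25% against 20% gives z = 0.05/√(0.225×0.775×2/812) ≈ 2.4, P ≈ .016. That passes P≤.15, and a strong predictor would not normally worsen model fit. This stands on the condition that the variable is a candidate in that province, which the plan does not secure.

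**A condensed article may leave the covariate list to a fuller document.** That is fair for the detail of the list. But the article itself states the fixed set, the entry rule for the second set and the adjustment screen. Under those rules, two groups of outcome baselines are left to data-driven selection, while ADLh and CPS are not.

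**Conclusion.** The point holds as a missing commitment. Neither the index DRS score nor pre-index emergency, hospital and primary care use is named for matching or adjustment, although both are baselines of stated outcomes, are available in the linked data, and belong to outcomes not defined as change. Balance on them is therefore possible but not assured, and how they are handled may differ by province.

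The size of any bias is unknown. The odds ratios of 1.10 to 1.30 and rate ratios of 1.04 to 1.19 show what would follow if the assumed imbalance existed, remained after matching and went unadjusted; they are not estimates. The article's statement that its approach ensures comparable groups at baseline is supported by the named covariates for ADLh and CPS, but not for mood or service use. This should be settled before matching is run.

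**What to change.** Take one of two routes, in all three provinces:

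1. **Matching.** Name as required propensity covariates the DRS score at the index RAI-HC and the counts of emergency visits, hospital admissions, hospital days and primary care visits in a fixed window before index, for example 12 months.
2. **Adjustment.** Force the index value of each outcome (index DRS, or the pre-index count of the same service) into its objective 3 model, outside the P≤.15 and stepwise rules.

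Under either route, report balance on these variables after matching, by province. In British Columbia, build pre-index emergency counts from the same sources as the outcome (NACRS and the physician payment file).

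The cost is small. The variables are in files already being linked, and the article says potential matches far exceed attendees, so only a few matches should be lost. People with an index date early in 2012 will need a shorter look-back, or service records from before 2012. No sample size figure changes.

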### Setting and Sample

Our study settings are community-based continuing care systems. Each province provides access to a range of publicly funded community-based continuing care services, including adult day programs [55-63]. Each provincial health system determines and enacts access criteria and provides services (directly or via contracted providers) [55-63]. Day program eligibility is assessed in each province, using comparable processes, criteria, and assessments (ie, the Resident Assessment Instrument—Home Care [RAI-HC], a standardized, valid, reliable assessment tool [64]) [60,65,66]. To be eligible, attendees need to have not only some care dependency but also the ability to cope to some extent with activities of daily living, ambulate or transfer with no or minimal assistance, be continent or independent in managing continence products, exhibit no or easily manageable responsive behaviors, and either be alone for extended periods or have a caregiver who requires respite. Our study cohort will include all individuals aged 65 years or older with an initial RAI-HC assessment completed between January 1, 2012, and December 31, 2021. We will follow everyone until they move into a care home, are lost to follow-up (eg, because of death, moving out of province, loss of public insurance eligibility), or until December 31, 2024 (the end of the period covered by our data). That will allow for a care trajectory of at least 3 years (for those with an initial RAI-HC assessment in December 2021), enabling us to assess the number and characteristics of individuals with different day program use patterns, and compare them with those who were never exposed to a day program.

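### Propensity matching as described cannot ensure that controls were eligible for a day program: no eligibility rule is applied, and two stated criteria have no named matching variable

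*Protocol article*

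**What the plan says.** Setting and Sample lists what an attendee must satisfy. There must be some care dependency with some ability to cope with daily activities, and continence or independence with continence products. Responsive behaviours must be absent or easily manageable. The person must also "ambulate or transfer with no or minimal assistance" and "either be alone for extended periods or have a caregiver who requires respite".

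Propensity Score–Matching Variables names a first set of matching covariates, described as those the health systems use to decide eligibility: the ADLh Scale, the CPS, the Aggressive Behavior Scale, continence items I1 and I3, caregiver availability (G1e) and caregiver distress (G2a-c). It then states: "This will ensure that control participants are potentially eligible to a day program". A few sentences later: "This approach excludes individuals whose care needs are either too low or too severe for day program eligibility".

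The cohort itself is not restricted by eligibility: "Our study cohort will include all individuals aged 65 years or older with an initial RAI-HC assessment" completed in the accrual window. Candidate controls for an attendee are nonattendees whose first RAI-HC falls within three months either side of the attendee's index date. Objective 3 fits one logistic regression per province and matches 1:1 without replacement, using a caliper of 0.2 SD of the logit. Score quintiles are the fallback if too few matches result.

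**The concern.** Two affirmative claims, that matching secures eligibility and that it removes ineligible people, do not follow from the procedure. Objective 3 is meant to compare attendees with people who could have attended but did not. If some controls could not have attended, the contrast partly reflects the eligibility decision rather than the program. Time to care home admission is exposed to this, because needs too severe for a day program, and being alone for long periods, plausibly bear on admission as well.

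**Working it through.** The plan gives no figure on this point, so there is none to reproduce. The check has three steps.

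**1. Is anyone removed by criterion?** Before matching, the limits on a control are age 65 or older, an initial RAI-HC in the accrual window, no day program exposure, and the three-month window. None is an eligibility rule. In matching, with logit(p) = b0 + Σ b_k x_k, persons i and j may be paired when

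|Σ b_k (x_ik − x_jk)| ≤ 0.2 × SD(logit).

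This bounds a sum, not any one x_k. A nonattendee over the limit on one criterion can be paired if other covariates offset it. Quintiles loosen the bound further. The plan also picks its second covariate set by comparing attendees with potentially eligible nonattendees, but describes no step that forms that group. Objective 2 uses the full cohort.

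**2. Is every criterion represented?**

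| Criterion (Setting and Sample) | Named in the first matching set |
|---|---|
| Care dependency, coping with daily activities | ADLh, CPS |
| Ambulation or transfer | none; ADLh as partial proxy |
| Continence, or independent with products | I1, I3 |
| Responsive behaviours | Aggressive Behavior Scale |
| Alone for extended periods, or caregiver needs respite | G1e and G2a-c for the caregiver half; time alone not named, G1e as partial proxy |

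The last row matters despite being an either/or. An eligible attendee whose caregiver does not need respite must be alone for extended periods. A control with identical caregiver items need not be.

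**3. How large could it be?** Every input here is an assumption.

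*Time alone only.* Let a be the share alone for extended periods and c the share with a caregiver needing respite. Take these as independent, all attendees as meeting the criterion, and controls as matched exactly on respite need but not on time alone. The share of controls failing is

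[a(1 − c) / (c + a(1 − c))] × (1 − a).

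- a = 0.4, c = 0.4: (0.24/0.64) × 0.6 = 0.375 × 0.6 = 22.5%
- a = 0.4, c = 0.2: (0.32/0.52) × 0.6 = 36.9%
- a = 0.4, c = 0.6: (0.16/0.76) × 0.6 = 12.6%
- a = 0.9, c = 0.6: (0.36/0.96) × 0.1 = 3.8%

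*All criteria, by simulation.* 40,000 people per run; attendance 3% or 8%, drawn only from the eligible; correlation between dimensions 0 or 0.3; assumed cut-offs; 75–83% of the control pool ineligible; nearest-neighbour 1:1 matching within the 0.2 SD caliper.

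| Score and matching | Controls failing a measured criterion | Controls failing any criterion, with mobility and time alone counted |
|---|---|---|
| First set only, linear or categorical terms | 0–1% | 36–46% |
| Plus age, sex, deprivation; linear terms | 19–25% | 50–59% |
| Plus age, sex, deprivation; categorical terms | 3–5% | 39–48% |
| Same covariates, quintile fallback, either form | 16–30% | 44–63% |

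*A second assumed set-up* had 60,000 people, 5,646 attendees, five severity dimensions and ineligibility above 1.3 SD on any. With linear terms and independent dimensions, two implementations put 41% and 33% of matched controls over a severity cut. The second gave 21% at correlation 0.3 and 14% at 0.6. Seven-level categorical terms gave 0% in all three cases, although one category boundary sat at the cut, which favours that result. About 23–26% still failed overall, all through the alone-or-respite criterion with both prevalences set at 40%. That is close to the 22.5% above.

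**The case against.** The article says only *potentially* eligible, and its statement that people are excluded could be read as implying a restriction whose cut-offs sit in a fuller plan. The covariate list is not final: Objective 2 informs it, and the second set is open, so mobility or living situation could still enter. ADLh and caregiver availability carry part of the missing information, and Data Sources mentions whether the caregiver lives with the person. Matching also makes grossly ineligible controls much less likely: with the first set alone, almost none failed a measured criterion in the illustration.

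Much of this stands, and it limits the size of the point. It does not rescue the two claims. The sentence on ensuring eligibility refers to the matching covariates just listed, not to a separate filter, and no section describes one. Covariates that might be added later cannot support a present claim that eligibility is secured.

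A reader might go further and infer that a large, known share of controls will be ineligible and that this favours day programs. The document supports neither. The share depends on the score's functional form and on how common the criteria without a named variable are. As for direction, controls with needs too severe would plausibly enter care homes sooner, but controls with needs too low would push the other way. In the second set-up (linear, independent dimensions), mean summed severity was −0.89 in matched controls and −0.92 in attendees, against +0.08 in the pool, so controls extreme on one dimension were milder on others. No outcome was simulated. Objective 3 also allows adjustment for time-varying covariates, though adjustment does not make an ineligible person eligible.

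**Conclusion.** The point holds as a mismatch between claim and method. Matching on the described score makes eligible controls more likely. It does not ensure them and excludes nobody by criterion, and two of the plan's own criteria are covered only by proxies. Ineligible nonattendees can therefore enter the comparison group.

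The number of such controls and the direction of any bias cannot be determined from the document. The simulated percentages rest on invented distributions, cut-offs and prevalences, and on attendees being eligible by construction, so the contrast with attendees is built in. They show two things. Failures on measured criteria can be made small by the choice of covariates and terms. Failures on criteria with no named variable persisted in every scenario simulated. This should be settled before matching, because it decides who the controls are.

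**What to change.** Before fitting the propensity model:

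1. Turn the plan's own eligibility criteria into explicit rules, using the RAI-HC items the provinces already use for this decision. The criteria are worded qualitatively, so the provincial partners must supply the cut-offs.
2. Apply the rules identically to attendees, at the index assessment, and to nonattendees. Filtering nonattendees alone would create a new asymmetry if some real attendees fail a recorded criterion.
3. Add mobility or transfer and time-alone variables to the first matching set where they are recorded. Data Sources names neither, so availability must be confirmed.
4. Enter the eligibility scales as categorical terms. In the illustration with age, sex and deprivation added, this cut failures on measured criteria from 19–25% to 3–5%.
5. For any criterion that cannot be applied, replace the wording on ensuring and excluding with a statement that matching makes eligibility more likely, and list the gap as a limitation.

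The cost is a smaller control pool, which the plan reports its experts expect to be much larger than the number of attendees. A few attendees who do not meet the recorded criteria may be lost, and each province has modest extra analysis work.
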